### Primary outcome measures

The co-primary outcome measures will be the Social Phobia Scale [SPS; [52]], a 20-item self-report measure of the respondent’s characteristic or typical fear of negative evaluation in social performance situations (e.g. public speaking, eating in front of others), and its companion measure, the Social Interaction Anxiety Scale [SIAS; [52]], a 20-item measure of anxiety related to social interactions (e.g. attending parties). These scales are frequently administered in tandem to comprehensively assess for both of these major components of social anxiety [58]. Both scales are widely used in clinical research, with studies demonstrating evidence of internal consistency (*α* = 0.89–0.94), test–retest reliability (*r* = 0.91–0.93) [52, 59], and construct validity, including concurrent validity, discriminant validity, and treatment sensitivity [52, 57–65].

### Secondary outcome measures

Patient Health Questionnaire-9 [PHQ-9; [53]]: The PHQ-9 is a 9-item, widely used, reliable and valid measure of depression symptom severity over the past 2 weeks [43, 66, 67]. Evidence of internal consistency (*α* = 0.86–0.92), test–retest reliability (*r* = 0.84), sensitivity and specificity (both 0.88), and construct, convergent, and discriminant validity, as well as treatment sensitivity have been reported [66–70].

Work and Social Adjustment Scale [WSAS; [71]]: The WSAS is a 5-item measure of quality of life and interference in the domains of work, home management, leisure activities, and close relationships. In clinical samples, evidence of internal consistency (*α* = 0.70–0.94), test–retest reliability (*r* = 0.73), convergent and discriminant validity, and treatment sensitivity has been provided [71–73].

Level of Personality Functioning Scale—Brief Form 2.0 [LPFS-BF 2.0; [74]]: The LPFS-BF 2.0 is a 12-item measure of level of personality functioning in the domains of self (identify and self-direction) and other (empathy and intimacy). It has demonstrated internal consistency (*α* = 0.82), discriminant validity, construct validity, and sensitivity to change over treatment, and has been validated in varying clinical, forensic, and community samples worldwide [74–78].

Personality Inventory for DSM-5—Brief Form [PID-5; [79]]: The PID-5-BF is a 25-item measure of the following personality trait domains: negative affect, detachment, antagonism, disinhibition, and psychoticism. For the each of the facets, internal consistency [*α* = 0.72–0.96 [79]], test–retest reliability (*r* = 0.57–0.87), construct validity, structural validity, and convergent validity have been demonstrated [80–84]. Both the LPFS-BF 2.0 and PID-5-BF were administered at baseline and 1-month follow-up only due to the impact of the relatively short time period on test–retest reliability and treatment sensitivity [67, 78], and to reduce participant burden.

Credibility/Expectancy Questionnaire [CEQ; [85]]: The first four items of the CEQ measures participants’ perception of the credibility and expected perceived benefit of a treatment before its commencement. It has been shown to possess internal consistency across several studies [*α* = 0.85–0.90; [85–87]], as well as temporal stability, and predictive validity for treatment outcome [85].

Bespoke questions about health service use (HSU): Including participants’ current psychotropic medication use, previous experience of treatment for anxiety or depression, and level of experience with CBT.

### Additional outcome measures

Participants in the treatment group will be administered additional questionnaires to assess the acceptability, treatment satisfaction, treatment engagement, feasibility, and side effects of the intervention.

Module feedback: Prior to starting each lesson, participants will be asked to provide brief feedback about the previous module with the question ‘Do you have any feedback (positive or negative) about the previous lesson that you would like to share with us? Please be honest as it helps us to improve the program’.

Strategy use: Participants will be asked about the frequency with which they have used each strategy (e.g. ‘using video feedback’ or ‘thought challenging’; from 0 = never to 5 = very often), and an open-ended question asking which strategy they feel was most helpful in reducing their fear of social situations.

Treatment Satisfaction Questionnaire [TSQ; [88]]: the TSQ is a 5-item measure of treatment satisfaction used frequently in RCT studies evaluating CBT treatments [e.g. [89–91]]. It prompts participants to rate on a series of Likert scales their overall level of satisfaction with the treatment, the pace of the treatment, how logical it seemed, how confident they were that the program was successful in teaching them skills to manage their anxiety, and how confident they would be in recommending the treatment to a friend with similar symptoms.

Side effects: At post-treatment, participants will be asked to describe any positive effects or events and any unwanted side effects or negative events they feel occurred because of the program. Prior to starting each module, participants will also be asked if they experienced any difficult or adverse events since the last lesson.

Further open-ended questions will be included in post-treatment questionnaires regarding participants’ treatment experiences, including which aspects of the treatment they found most helpful and unhelpful and that they liked and disliked the most; how the program could be improved; how relatable they found the characters; how the characters could be improved to be more relatable to them; and any further comments.

Further qualitative questions regarding participants’ experience of the program will be asked in the 1-month follow-up interview, including their overall experience of using the program; their opinion of the strategies suggested; whether there were any other topics they would have liked covered in the program; any suggested changes to the program; what they liked most and least about the program; and any further feedback. These questions are included to ensure participants have an opportunity provide their feedback and provide suggestions on how to improve the program. This information will be used to inform refinements and improvements to the program and treatment model before any further studies are conducted.

We will measure adherence using rates of program completion (i.e. the total number of modules completed out of 6) and engagement by asking participants to self-report approximately how many minutes they spent reading the previous module materials and how many minutes they spent practising the skills in the previous day. These questions are also asked at the conclusion of module 6. Further qualitative questions around engagement in the 1-month follow-up interview will be asked, including whether participants continue to use any strategies from the program (and which ones); any changes in behaviours that have occurred since using the program; what contributed to their continued engagement; and any barriers to engagement that they experienced and suggestions for reducing these barriers.

### Statistical analysis

All analyses will be undertaken using intention-to-treat approach. Linear mixed models, with a random intercept for subject will be used to analyse primary and secondary outcomes, and covariances matrixes used to assess relationships between variables. This approach will be used to manage missing data and account for correlation between repeated measures. Before conducting the analyses, patterns of missing data will be assessed through data visualisation, and Little’s Missing Completely at Random (MCAR) test to determine whether the data are missing at random. If there are significant group differences (as determined by independent samples *t*-tests) in the amount of time elapsed between the intake interview and completion of baseline measures, this variable will be included as a covariate in the linear mixed models. Planned contrasts will be used to compare pre- and post-treatment, and pre-treatment and 1-month follow-up, and planned pairwise comparisons will be used to compare between-groups at post-treatment and follow-up. To control for the risk of type 1 error with a co-primary outcome, the alpha level for significance will be adjusted using a Bonferroni correction (alpha set at 0.025 to determine statistical significance for the SIAS and SPS co-primary outcome measures). Linear mixed models will be utilised to test the predictors of treatment outcome. Within- and between-group effect sizes will be calculated using Hedges’ *g* (with 95% confidence intervals) to estimate the within-group changes from baseline to post-treatment, and baseline to follow-up, and between-group differences on primary and secondary outcome measures at post-treatment and follow-up.

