### Trial aims and hypotheses

This protocol has been reported according to SPIRIT guidelines for reporting of trial protocols [50, 51]. The primary aim of this study is to investigate the efficacy of the intensive iCBT for SAD program [44] in improving symptoms of social anxiety at post-treatment and 6-week follow-up, relative to a WLC group. The secondary objectives of the trial are to evaluate the efficacy of the program in reducing symptoms of depression and functional impairment/quality of life at post-treatment and follow-up. A third aim is to further explore the program’s acceptability and feasibility. We aimed to test whether the strong adherence and satisfaction observed in the pilot trial were replicated in a larger sample and outside of the COVID-19 pandemic context. A fourth aim is to explore predictors of treatment effectiveness, including participant age, gender, baseline symptom severity, and personality.

The primary hypothesis is that participants who receive the intensive iCBT for SAD intervention will show significantly reduced social anxiety symptom severity compared to the WLC group. We also hypothesise that intensive iCBT for SAD will be significantly more effective at improving participants’ comorbid depressive symptoms and increasing quality of life relative to the WLC group. The third hypothesis being tested is that intensive iCBT for SAD will be acceptable to participants according to high adherence (> 80%) and treatment satisfaction ratings. A further set of exploratory analyses will investigate whether the effectiveness of the intervention is predicted by participant age, baseline symptom severity, and personality functioning.

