### Sample size calculations

The planned sample size is 50 participants, with participants randomly allocated to either a treatment group (*n* = 25) or a waitlist control group (*n* = 25). Power calculations are based on an estimated between-group effect size of 0.92 based on a meta-analysis of iCBT compared to controls [92] with alpha set at 0.05 and power at 0.8. A minimum sample of 20 participants per group is required to detect this effect size. An additional 5 participants per group will be recruited to account for expected attrition based on our pilot trial [33].

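### A subject random intercept alone understates the uncertainty of pre-post change in the iCBT arm if response varies between patients; the primary between-group comparison at T2 is little affected

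*Protocol article*

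**What the plan says.** The Statistical analysis section of the protocol article gives the model as follows: "Linear mixed models, with a random intercept for subject will be used to analyse primary and secondary outcomes". It adds "covariances matrixes used to assess relationships between variables" and then says that the approach is meant to deal with missing data and with correlation among the repeated measurements. It names no random slope, no residual structure over visits and no variance that differs by arm.

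Two sets of comparisons follow. The first is "Planned contrasts will be used to compare pre- and post-treatment, and pre-treatment and 1-month follow-up". The second is "planned pairwise comparisons will be used to compare between-groups at post-treatment and follow-up". Significance for the co-primary scales is fixed in the words "alpha set at 0.025 to determine statistical significance for the SIAS and SPS co-primary outcome measures". The same section promises within-group and between-group Hedges' g with 95% confidence intervals.

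Two other sections bear on the choice. Primary outcome measures cites a test-retest correlation of 0.91 to 0.93 for the SIAS and SPS. Trial aims and hypotheses says: "A fourth aim is to explore predictors of treatment effectiveness".

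**The concern.** A random intercept with independent residuals implies compound symmetry. Change from T1 to T2 under treatment is then assumed to vary no more than change on the waitlist, and no more than change from T2 to T3 once treatment is over.

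The protocol's own premises sit badly with that. A test-retest correlation above 0.9 means that untreated scores should barely move. An aim to find predictors of benefit makes sense only if patients may differ in how much they gain. Together these suggest that change is more variable in the treated arm than on the waitlist.

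If so, the model averages a large change variance with smaller ones. Model-based tests and intervals for iCBT change become too optimistic, and those for the waitlist too cautious. These contrasts matter for reading the trial against the uncontrolled pilot, whose symptom results could only be pre-post change. The alpha of 0.025, adopted to control type 1 error, would not hold for them.

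**Working it through.** The plan gives no figure for the error rate of these contrasts. Its nearby figure, 20 per group for an effect of 0.92 at alpha 0.05 and power 0.8, reproduces with a two-sided t-test (power 0.809) and is not in dispute.

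**Inputs from the document:** 25 per arm; visits T1, T2 and T3; alpha 0.025 per co-primary scale; between-visit correlation r = 0.92, the middle of the cited 0.91 to 0.93.

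**Assumptions:** baseline SD 1; complete data; true mean change 0; an individual response with SD τ, added equally at T2 and T3 in the iCBT arm only. The document gives no τ, so it is varied, and r = 0.8 and 0.7 are run as well.

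**Variance of change.** Residual variance is 1 − r = 0.08, so a difference between two visits has variance 2 × 0.08 = 0.16 without any response variation.

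- True variance of iCBT T1-T2 change: 0.16 + τ².
- Value the model uses: the average over the three visit pairs, then over the two arms. In the iCBT arm, T1-T2 and T1-T3 each have 0.16 + τ² and T2-T3 has 0.16, giving 0.16 + 2τ²/3. On the waitlist it is 0.16. The average of the two arms is 0.16 + τ²/3.
- Ratio R = (0.16 + τ²) / (0.16 + τ²/3).

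At τ = 0.5: 0.16 + 0.25 = 0.41 is true and 0.16 + 0.083 = 0.243 is used. R = 1.685, and the standard error is 1 − √(0.243/0.41) = 23% too small.

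**Rejection rate.** Approximately 2 × [1 − Φ(t/√R)], with t = 2.277 (96 df, two-sided 0.025). Simulation of 40,000 trials per setting gives:

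| r = 0.92, nominal 0.025 | τ = 0.3 | τ = 0.5 | τ = 0.7 |
|---|---|---|---|
| R | 1.316 | 1.685 | 2.010 |
| Standard error too small by | 13% | 23% | 30% |
| iCBT T1-T2, formula | 0.047 | 0.079 | 0.108 |
| iCBT T1-T2, simulated | 0.050 | 0.084 | 0.112 |
| Waitlist T1-T2, simulated | 0.014 | 0.006 | 0.002 |

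Separate simulation runs at τ = 0.5 gave 0.081 to 0.086. At nominal 0.05 the iCBT contrast rejects at 0.089, 0.131 and 0.165.

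**Sensitivity at nominal 0.025.**

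- τ = 0: nominal.
- r = 0.8, τ = 0.5: about 0.052. r = 0.7, τ = 0.5: about 0.044. Across runs the two span about 0.044 to 0.054.
- If individual responses at T2 and T3 correlate 0.7 rather than 1 (r = 0.92, τ = 0.5): 0.069.
- Group-by-time contrast, r = 0.92: at τ = 0.5 the true variance is 0.41 + 0.16 = 0.57 against 2 × 0.243 = 0.487, a ratio of 1.17. The simulated rate over τ = 0.3 to 0.7 is about 0.031 to 0.045.
- Between-group test at T2, r = 0.92: 0.027 to 0.031.

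**Where the error comes from** (r = 0.92, τ = 0.5, nominal 0.025).

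- Random intercept fitted in the iCBT arm alone: it uses 0.16 + 2 × 0.25/3 = 0.327 against 0.41 and rejects at 0.046.
- Unstructured covariance common to both arms: it uses (0.41 + 0.16)/2 = 0.285 and rejects at 0.060.
- Arm-specific unstructured or paired contrast: it rejects at 0.026 (0.050 at nominal 0.05).

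So both compound symmetry across visits and pooling with the waitlist contribute, and removing only one is not enough.

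**The case against.** Several points on the other side stand.

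- **Residual structure.** The article never states independent residuals or a single residual variance. A random intercept can be combined with a residual structure, and the SAP, which is not shown, may do so. The covariance phrase is unclear, but it speaks of variables and names no visit or arm structure. The concern is therefore with the usual reading of the published wording.
- **Per-arm contrasts.** The text does not say that the pre-post contrasts are within arm. That is the likelier reading, because they are listed apart from the between-group comparisons and cover the same intervals as the within-group effect sizes. It is not explicit, and on the group-by-time reading the inflation is mild.
- **Remote null.** The pilot reported g of 1.26 to 1.9 for social anxiety. With the correct variance at τ = 0.5, the standard error is √(0.41/25) = 0.128; a change of half the lower pilot value, 0.63, gives t of about 4.9. Whether iCBT change is significant would probably not turn on this. The stated precision would.
- **Intervals.** The only intervals promised are those for Hedges' g, and nothing says that they use the model's residual variance. The point applies to model-based change estimates.
- **Correlation.** Participants are selected on high SIAS and SPS scores, which could lower the between-visit correlation and shrink the effect.

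A reader might infer that the error rate is 2 to 4 times alpha whenever patients differ in response. The document does not support that: at r = 0.92 and nominal 0.025 it takes a response SD of about 0.32 to 0.64 baseline SD, and the document gives none. A reader might also infer that the primary result is unsafe. The primary hypothesis is between-group, with T2 as the primary time point, and that test stays close to nominal.

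**Conclusion.** The point holds in conditional form. On the usual reading of the stated model, the iCBT arm's change is given too small a standard error and the waitlist's change too large a one, provided that response varies between treated patients. At 25 per arm and r = 0.92, the iCBT T1-T2 contrast rejects at about two to four and a half times the nominal 0.025 for an assumed response SD of 0.3 to 0.7 baseline SD (0.050/0.025 = 2.0; 0.112/0.025 = 4.5). The excess shrinks with a lower correlation, a less persistent response or a group-by-time reading, and vanishes without response variation. All figures assume complete data. This is a minor-to-moderate weakness in supportive within-arm results and does not threaten the primary efficacy conclusion.

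**What to change.** Replace the random intercept with an unstructured covariance over T1, T2 and T3, using Kenward-Roger or Satterthwaite degrees of freedom. Take within-arm T1-T2 and T1-T3 estimates and intervals from an arm-specific unstructured covariance. If the software cannot fit that, use an unstructured model or a paired contrast within the arm. A random-intercept model fitted in one arm does not solve the problem. State whether the planned pre-post contrasts are within arm or group-by-time.

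No new data are needed. The costs are:

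- Covariance parameters rise from 2 to 12 (6 per arm), which should be estimable with three visits and about 25 per arm.
- Within-arm degrees of freedom fall, with complete data, from about 96 (48 × 2) to about 24 (25 − 1).
- Intervals for iCBT change become wider.

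Trial status says that analysis is already underway, so the change should be reported as a documented deviation or as a sensitivity analysis beside the published model.

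### Little's MCAR test is given the task of showing whether data are missing at random, which it cannot do, so its result could give false assurance about the assumption behind the mixed models

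*Protocol article*

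**What the plan says.** All of the relevant text is in the Protocol article, mostly under Statistical analysis.

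- **Model:** "Linear mixed models, with a random intercept for subject will be used to analyse primary and secondary outcomes". Of this choice the article says: "This approach will be used to manage missing data and account for correlation between repeated measures". The predictor analyses use the same class of model: "Linear mixed models will be utilised to test the predictors of treatment outcome".
- **Checks before analysis:** one is descriptive: "patterns of missing data will be assessed through data visualisation". The other is a formal test, the one due to Little, which the article describes as a "Missing Completely at Random (MCAR) test to determine whether the data are missing at random".
- **Consequence of the checks:** none is stated. No analysis choice is tied to the test result.
- **Expected loss (Sample size calculations):** "The planned sample size is 50 participants", 25 per arm. "A minimum sample of 20 participants per group is required to detect this effect size", and to this figure the plan adds a margin: "An additional 5 participants per group will be recruited to account for expected attrition".
- **Timing:** T2, at 2 weeks, is the primary time point (Trial design and setting). SIAS, SPS and PHQ-9 are collected at T0, T1, T2 and T3 (Table 2).

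**The concern.** A likelihood-based mixed model gives valid estimates with incomplete outcomes if the data are MAR given what is in the model. Whether MAR or MNAR holds depends on values nobody has seen, so no test on the observed data can decide it. Little's test addresses a different and narrower question: whether the observed means differ between missingness patterns by more than MCAR allows.

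The purpose given to the test is therefore wrong whichever way it falls. A rejection is compatible with MAR, where the model is valid. A non-rejection is compatible with MNAR, where it is biased.

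The article itself makes informative dropout plausible. The programme asks for 3–4 hours of practice a day. The Background says that some participants in intensive iCBT felt overwhelmed by the pace. The safety section offers withdrawal to those the study distresses. A treated participant lost before T2 who does not return contributes only pre-treatment SIAS and SPS scores, so nothing observed on those scales shows how that person responded. At stake is what a reader may conclude about the robustness of the T2 result if a non-significant test in 50 people is taken as evidence for MAR.

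**Working it through.** **1. The plan's own figure.** Inputs from Sample size calculations: effect 0.92 SD, alpha 0.05 (taken as two-sided), power 0.80. The exact two-sample t calculation gives 19.55, rounded up to 20 per group, with power 0.809 at 20. Allowing for 20% loss, 20 / 0.80 = 25. The figure reproduces, and the allowance is 5/25 = 20% per arm. The point below does not depend on it.

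**2. What each test result can mean.**

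| Little's test | Compatible with | Mixed model |
|---|---|---|
| Not significant | MCAR, MAR (low power) or MNAR | valid, valid, biased |
| Significant | MAR or MNAR | valid, biased |

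Neither row separates MAR from MNAR.

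**3. Behaviour at this sample size.** Two simulations used 25 per arm, three waves, effect 0.92 SD, about 20% dropout after baseline, 600 runs per scenario and a 5% test level. The correlations and dropout mechanisms are assumptions; the article supplies none. The treatment estimate was a baseline-adjusted one on observed cases, standing in for the planned mixed model.

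*Simulation A: one scale, correlation over time 0.5 or 0.7.*

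| Dropout mechanism | Test rejects | T2 estimate (true −0.92) |
|---|---|---|
| MCAR | 5–6% | −0.92 |
| MAR: depends on baseline, log-odds 1 per SD | about 70% | −0.92 to −0.93 |
| MNAR: treated participants with worse unseen T2 scores leave | 4–5% | −1.11 to −1.13 |

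The MNAR bias is 1.11 − 0.92 = 0.19 to 1.13 − 0.92 = 0.21 SD in favour of treatment.

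*Simulation B: two scales, correlation 0.7 over time and 0.6 between scales.*

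| Dropout mechanism | Test rejects |
|---|---|
| MCAR | 4.3% |
| MAR: depends on baseline, odds ratio 2 per SD | 29.5% (estimate unbiased) |
| MNAR: depends on change | 9% |
| Treated dropouts gained nothing | 4% (estimate 0.92, full data 0.73) |

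The MAR rejection rate moves from about 30% to about 70% with the assumed set-up, so neither figure is a forecast for this trial. The pattern is common to both: the test rejects most often where the estimate is unbiased, and at or near its nominal level where the estimate is too favourable.

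**4. Illustrative size.** Let m be the fraction of treated participants with missing T2 data. Assume that they gained nothing relative to waitlist, that waitlist missingness is uninformative, and that the MAR estimate equals 0.92. Then

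effect in all randomised = (1 − m) × 0.92 + m × 0.

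- m = 0.20 (recruitment allowance): 0.80 × 0.92 = 0.736, about 0.74.
- m = 1/16 (pilot module non-completion, 15 of 16 completing): 15/16 × 0.92 = 0.8625, about 0.86.

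**The case against.** **Loose wording.** The sentence gives the test its full name and may end in shorthand for missing completely at random. That is possible, but it does not rescue the check: a correctly described MCAR test still neither supports nor challenges MAR.

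**Nothing hangs on the test.** This stands. The same mixed model is fitted either way, so no estimate, contrast or alpha changes. The article also states no rule for reporting the test as support for the primary result. The harm is therefore one of interpretation.

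**It is not the only check.** This also stands. Visualisation is named in the same sentence, so Little's test is the sole formal test and not the sole check. Visualisation cannot separate MAR from MNAR either.

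**The absence of an MNAR analysis.** A reader might infer that the trial has no analysis departing from MAR. The documents do not support that. This is a condensed article, an analysis plan that is not shown may contain one, and its absence here is not an error. The error is the purpose assigned to the test.

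**The numbers are assumed.** This stands too. The 20% is a recruitment allowance, not observed attrition. Stopping modules is not the same as missing T2 questionnaires, which are sent by automated email and analysed by intention to treat. The simulations did not fit the planned mixed model.

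**Conclusion.** The purpose stated for Little's test is wrong as written. The test cannot establish MAR, cannot contradict it and cannot identify MNAR dropout, so the one formal check named leaves untouched the assumption on which the primary, secondary and predictor models rely.

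The consequence is false assurance, not a different primary estimate. A reader might go further and infer that the T2 effect will be inflated by some 0.2 SD. The documents do not show that. The gap between 0.92 and 0.74–0.86 illustrates what the test would not reveal if treated participants with missing data gained nothing. It shrinks towards zero as missingness falls or as those participants resemble the ones observed. That the test cannot do what is asked of it rests on none of these assumptions.

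**What to change.** 1. Describe Little's test as a check of MCAR only, or drop it.
2. State that the mixed models assume MAR and that the observed data cannot verify this.
3. Report missing T2 and T3 outcomes by arm and relate them to T0 and T1 SIAS, SPS and PHQ-9. T0 scores are collected before randomisation, so they should be available even for participants who never reach T1.
4. Judge robustness by one sensitivity analysis of the T2 SIAS and SPS contrasts. One option is a delta-adjusted tipping-point analysis, worsening the imputed iCBT scores until the result at the planned 0.025 level is lost. The other is reference-based multiple imputation that draws missing iCBT outcomes from the waitlist trajectory. Either serves; choose one and name it.
5. Under Trial status, data collection had ended by the end of July 2024 and analysis was under way. If this analysis was not planned earlier, document it as added after data collection.

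The cost is a few sentences and a small amount of work on data already collected. The sensitivity estimate will usually be less favourable than the MAR estimate.
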